## Methods/Design

### Design

This study is a prospective non-randomized phase II trial of weekly irinotecan in patients with locally advanced or metastatic HER2- negative BC and increased copy numbers of the *TOP1* gene in their cancer cells.

#### Participants

The study is a multi-centre trial including 7 oncologic centres in Denmark. To be eligible for inclusion patients must provide written informed consent before any study related procedures. All patients must be above the age of 18, have performance status 0–2 according to the Eastern Cooperative Oncology Group (ECOG) and a life expectancy of ≥ 3 months. Furthermore, patients should have HER2-negative mBC and measurable disease according to RECIST 1.1 and with a maximum of 4 prior chemotherapy regimens for metastatic disease; all previous endocrine treatment is allowed. A neutrophil count of ≥ 1.5 x 10^9^ and platelets ≥ 100 x 10^9^ are required as well as adequate liver function. Finally, patients should have increased copy number of the *TOP1* gene in either their primary or metastatic lesion defined as ≥ 4 gene copy numbers or a *TOP1*/CEN-20 ratio of ≥2.

Exclusion criteria include current or previous other malignant diseases except basal cell carcinoma of the skin and carcinoma in situ cervices uteri, cytotoxic or experimental therapy within 14 days before enrolment and evidence of active CNS metastases. Furthermore, patients who are pregnant, breastfeeding or of childbearing potential and not using adequate non-hormonal contraception will be excluded as will patients with active infections or other severe concomitant medical conditions that may hinder the patient’s opportunity of receiving treatment according to the protocol.

#### Treatment

Patients are treated with irinotecan 75 mg/m^2^ weekly for three weeks followed by two weeks break. CT scans are performed prior to initiation of treatment and then every 6 weeks. Treatment is continued until progression or unacceptable toxicity. Toxicity is assessed prior to every treatment according to the common terminology criteria for adverse events (CTCAE, version 4.0).

#### Ethics

The trial was approved by the Ethical Committee of Region Hovedstaden (H-1-2012-066) as well as by the Danish Medical Authority (EudraCT number 2012-002348-26) and the Danish Data Protection Agency (2007-58-0015 /HEH.750.24-64).

#### Study objectives

The primary end point of this study is clinical benefit rate (CBR) defined as the fraction of patients receiving clinical benefit (CB) in the form of complete or partial response or stable disease ≥ 4 months according to RECIST 1.1. Secondary endpoints include PFS, OS and toxicity.

#### Statistics

Number of patients in the study is based on Simon’s two-stage minimax design. Intention-to-treat analysis will be performed. By using a significance level of 0.05 (a = 0.05) and a power of 80% (b = 0.20) 19 patients should be included in the first step in order to find a CBR of at least 30%. Further inclusion ceases if less than 7/19 patients show CB. If 7 or more show CB another 20 patients will be included. If more than a total of 16 patients achieve CB the hypothesis is satisfied.

PFS and OS will be estimated using the Kaplan-Meier method and compared with a log-rank test. Categorical variables are indicated by a median followed by the span. A significance level of 5% will be used. PFS and OS will be assessed in the evaluable population.

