**Methods/Design:**

This multi-centre phase II single arm trial was designed to investigate if patients with metastatic breast cancer and increased expression of the topoisomerase 1 gene have a high likelihood of obtaining a clinical benefit from treatment with irinotecan. Trial recruitment is two-staged as 19 patients are planned to participate in the first part. If less than 7 patients have clinical benefit the trial stops, if more than 7 patients have clinical benefit a total of 40 patients will be included.

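### The sample-size statement presents the null rate (CBR 30%) as the rate to be found and never states the alternative; at 30% the stated rule succeeds about 5% of the time, not 80%

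*Protocol article*

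**What the plan says.** The Statistics section names the design ("Number of patients in the study is based on Simon’s two-stage minimax design") and sets the error rates: "By using a significance level of 0.05 (a = 0.05) and a power of 80% (b = 0.20"). The same sentence then gives the only rate in the design: "19 patients should be included in the first step in order to find a CBR of at least 30" per cent.

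The decision rule follows. At stage 1: "Further inclusion ceases if less than 7/19 patients show CB". Otherwise: "If 7 or more show CB another 20 patients will be included", which makes 39 in total. At the end: "If more than a total of 16 patients achieve CB the hypothesis is satisfied". The hypothesis is not put in numbers, 30% is not called a null or uninteresting rate, and no second CBR is given anywhere in the article.

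**The concern.** A Simon two-stage design needs two rates: a null rate, at which the type I error is controlled, and an alternative, at which the power holds. The article gives one, and its wording makes that one the rate to be found with 80% power. The boundaries do not fit this. Success needs at least 17 of 39 (43.6%), and even continuing past stage 1 needs 7 of 19 (36.8%). Both lie well above 30%.

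What is at stake is how the primary result is read:

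- **Planning.** A reader would think the trial can pick up a true CBR of 30 to 35%. In fact it will usually reject such a drug.
- **A negative result.** With 14 of 39 (35.9%) the trial fails its own rule, although the observed rate exceeds the only rate in print. One reader could call that a success; another could conclude that the CBR is below 30%. Neither follows.
- **Context.** The section on topoisomerase 1 in breast cancer puts the objective response rate to irinotecan at roughly 25-30%. CBR also counts stable disease of at least 4 months. It therefore matters whether 30% is the target or the rate to beat.

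**Working it through.** **Inputs, all from the Statistics section.** Stage 1: n1 = 19, stop at r1 = 6 or fewer. Stage 2: 20 more, n = 39. Success: more than r = 16. Significance level 0.05, power 0.80. Sidedness is not stated; one-sided is assumed, as is standard for a Simon design.

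**Formula.** For a true CBR p,

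P(success | p) = Σ over x = 7 to 19 of b(x; 19, p) × P(X2 > 16 − x), with X2 ~ Bin(20, p).

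P(stop at stage 1 | p) = P(X1 ≤ 6), with X1 ~ Bin(19, p).

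**Step 1: reproduce the stated design.** An exhaustive search for the minimax design (smallest n, then smallest expected n under the null) with level ≤ 0.05 and power ≥ 0.80, taking null 30% and alternative 50%, returns 6/19 and 16/39. These are exactly the article's boundaries. Type I error is 0.0455 and power 0.8036. The probability of stopping at stage 1 under the null is 0.6655, and the expected sample size under the null is 19 + 20 × (1 − 0.6655) = 25.7.

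**Step 2: try 30% as the alternative.** The same search gives different designs:

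| Null | Alternative | Minimax design |
|---|---|---|
| 5% | 30% | 0/7, 2/14 |
| 10% | 30% | 1/15, 5/25 |
| 15% | 30% | 3/23, 11/48 |
| **30%** | **50%** | **6/19, 16/39** |

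A neighbouring pair, 25% against 45%, gives 4/17, 13/36, which does not match either.

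**Step 3: what the stated rule does.**

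| True CBR | P(stop at stage 1) | P(success) |
|---|---|---|
| 25% | 0.825 | 0.008 |
| 30% | 0.666 | 0.0455 |
| 35% | 0.481 | 0.156 |
| 40% | 0.308 | 0.356 |
| 45% | 0.173 | 0.599 |
| 50% | 0.084 | 0.804 |
| 55% | 0.034 | 0.926 |

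The success probability reaches 5% at a CBR of 30.3% and 80% at 49.9%.

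**Step 4: a check that needs no search.** Success requires passing stage 1. At 30% that happens with probability 1 − 0.666 = 0.334, so power at 30% cannot exceed about 33% whatever the final cut-off. No choice of null rate can make the stated 80% true there.

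**The case against.** The strongest reply is that finding a CBR of at least 30% may simply mean showing that the CBR exceeds 30%. That is what rejecting a null of 30% does, and 30% would then be in its proper role. The sponsor may well have meant this. But on that reading the 80% power belongs to no stated rate and says nothing. The phrase also places 30% inside the range to be found, while the rule turns down a 30% drug about 95% of the time.

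A second reply is that an article condenses the full protocol, so an unstated alternative is no fault. Silence alone would indeed not be a finding. Here the article states the design type, level, power, both boundaries and one rate, and words that rate in the wrong role. That is a misstatement in the text shown.

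A third reply is that the boundaries are correct and explicit, so conduct does not depend on the sentence. This stands as far as it goes: no boundary, level or power figure is miscalculated, and a careful reader can recover the design. What depends on the sentence is the sensitivity claimed for the primary endpoint and the meaning of a negative result.

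It also stands that 50% is inferred. The document does not give it.

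**Conclusion.** The concern holds. The design is sound for 30% against 50%, but the text describing it is wrong: 30% is the type I error point, not the rate to be found. At the only rate printed, the probability of success is 4.55% against the 80% that the wording implies. At a true CBR of 35 to 40% the trial would fail 84% to 64% of the time (1 − 0.156 and 1 − 0.356). Power of 80% is reached only at about 50%.

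This rests on the boundaries as given in the Statistics section with 39 patients, exact binomial probabilities and a one-sided test. The success probabilities need no assumption about the intended alternative. Only the label of 50% is inferred, and it reproduces all four boundary numbers.

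**What to change.** Replace the sample-size sentence with wording such as:

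> Simon minimax two-stage design testing H0: CBR ≤ 30% against H1: CBR ≥ 50%, one-sided level 0.05 (exact 0.046), power 80% (exact 80.4%) at a CBR of 50%. The trial stops if 6 or fewer of 19 patients have clinical benefit; otherwise 20 more are enrolled, 39 in total. H0 is rejected if 17 or more of 39 have clinical benefit. With 16 or fewer, a CBR above 30% has not been shown.

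The sponsor should confirm the 50% from its design records before it is printed.

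The abstract should be aligned at the same time. It says "if more than 7 patients have clinical benefit a total of 40 patients will be included", which conflicts with 7 or more and 39 in the Statistics section and leaves exactly 7 undefined. This is a separate inconsistency, but it affects the restated figures: with 40 patients and the same cut-off, the type I error at 30% would be 0.056, above the stated 0.05.

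The cost is one rewritten sentence plus the alignment of the abstract. The boundaries and patient numbers in the Statistics section stay as they are. The price is candour: the detectable rate becomes 50% rather than an apparent 30%. The Trial status section reports 10 patients included, short of the 19 for stage 1, so at that point the correction could still precede the stage 1 decision.

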### Methods

#### TOP1 gene copy assessment

Prior to inclusion tissue samples from primary and/or metastatic lesions are investigated for *TOP1* and CEN20 gene copy numbers. Whenever possible, tissue microarrays (TMA) are constructed, using Advanced Tissue Arrayer, ATA-100 (Chemicon International, Temecula, CA, USA). Four 1 mm cores cut at 3 μm are obtained from each biopsy. Samples containing small amounts of tumor tissue or otherwise not suited for TMA construction have full sections made. FISH using a *TOP1*/Centromere-20 (CEN-20) probe [27,36] is used to evaluate the *TOP1*/CEN-20 ratio as well as the absolute number of *TOP1* gene copies per cell.

A total of 60 signals are counted per tissue sample. If a *TOP1*/CEN-20 ratio ≥2 or an absolute gene copy number of ≥4 is found the patient is eligible for inclusion.

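### PFS and OS are to be tested by log-rank in a single-arm trial that names no comparison groups, and categorical variables are to be summarised by a median and range

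*Protocol article*

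**What the plan says.** All places are in the protocol article.

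- **Abstract, Methods/Design:** "This multi-centre phase II single arm trial was designed".
- **Design:** "This study is a prospective non-randomized phase II trial of weekly irinotecan".
- **TOP1 gene copy assessment** (and, in similar terms, Participants): "If a *TOP1*/CEN-20 ratio ≥2 or an absolute gene copy number of ≥4 is found the patient is eligible for inclusion". Patients who meet neither criterion are not enrolled.
- **Treatment:** one irinotecan regimen for all patients. Toxicity is graded by CTCAE version 4.0.
- **Study objectives:** the primary endpoint is the clinical benefit rate. "Secondary endpoints include PFS, OS and toxicity".
- **Statistics:** "PFS and OS will be estimated using the Kaplan-Meier method and compared with a log-rank test", then "Categorical variables are indicated by a median followed by the span", then "A significance level of 5% will be used".

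No section names the groups, strata, external control or reference curve to which the log-rank test would apply.

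**The concern.** A standard log-rank test needs at least two groups, and this design supplies one. There is no control arm, and the eligibility rule removes the natural comparator, patients without increased TOP1. A named test at a named level with unnamed groups leaves the split open until the data are in. The trial's interest is in a predictive biomarker, so a p-value from a split chosen late could be read as evidence on that question when it is not.

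The sentence on categorical variables is a separate and smaller fault. Nominal categories have no median. Ordered categories do, but a median with its range does not give the number of patients in each category. That matters most for adverse events, because toxicity is a secondary endpoint and the Trial status section reports that the protocol was amended after two patients withdrew with severe diarrhoea.

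**Working it through.** **1. The plan's own design has one group.** The Statistics section gives a Simon minimax design: 19 patients, stop if fewer than 7 have clinical benefit, otherwise 20 more (19 + 20 = 39), success if more than 16 have benefit. An exhaustive minimax search with exact binomial probabilities, a null rate of 0.30 and an alternative of 0.50 (assumed, since the article does not state it) returns the same rule: 6/19 and 16/39, type I error 0.0455, power 0.804. This is a one-sample design and supplies no second group.

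**2. The log-rank test as written.** With k groups the test has k − 1 degrees of freedom. Here k = 1, so there are 0 degrees of freedom and no statistic.

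**3. What a split within the cohort could detect.** This is for scale only. Assumptions: two-sided 5%, and all 39 patients have an event. The second is an upper limit, because censoring or a smaller evaluable population would lower it. With d events and a fraction p in one group, Schoenfeld's formula for 80% power is

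|log HR| = (1.960 + 0.842) / √(d · p · (1 − p)).

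- Even split, d = 39: 2.802 / √(39 × 0.25) = 2.802 / 3.122 = 0.897, so HR = 0.41 (or 2.45).
- Even split, d = 40 (the Abstract's total): 2.802 / √10 = 0.886, so HR is again about 0.41.
- Approximately even split, d = 19 (trial stopped after stage 1): 2.802 / √4.75 = 1.286, so HR is about 0.28.

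Power at 39 events is Φ(|log HR| · √(39 · p · (1 − p)) − 1.960):

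| Split | HR 0.5 | HR 0.67 |
|---|---|---|
| 50:50 | 58% | 24% |
| 30:70 | 51% | 21% |
| 20:80 | 41% | 17% |

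For 80% power with equal groups, 66 events are needed at HR 0.5 and 196 at HR 0.67. Both exceed the planned number of patients.

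**4. Median and span applied to an ordered category.** With 39 patients the median is the 20th ordered value, so up to 19 of 39 (49%) could have a worst grade of 3 or higher while the median stays below 3. As an illustration, suppose some patients have grade 4 and all the rest grade 1. The summary is median 1, span 1 to 4, whether 1 of 39 (3%) or 19 of 39 (49%) had grade 4. The span shows that a severe event occurred, not how often.

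**The case against.** The strongest reply is that this is a condensed article. Subgroup definitions commonly sit in the full protocol or analysis plan, so failing to name them is no fault in itself. That is fair as far as it goes. What remains is that the article states an unqualified comparison of PFS and OS which the design it describes does not contain. That is a contradiction within the text, not a missing detail.

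Four stronger readings are tempting and are not supported:

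- **That no valid log-rank test is possible.** A test between baseline subgroups would be possible, for example between the two routes to eligibility, as would a one-sample test against a reference curve. The article names neither, so the claim is limited to the text as written.
- **That a responder versus non-responder comparison is planned.** No section proposes one. Such a split would be biased because the grouping is determined during follow-up. However, the four-month requirement in Study objectives attaches to stable disease only, so it would be wrong to say that every patient with clinical benefit must have been progression-free for four months.
- **That toxicity will be reported as a median grade.** The sentence does not mention toxicity. A median with range is the usual summary for continuous variables, so the wording is most likely a one-word slip. The loss of event frequencies follows only if the sentence is applied literally.
- **That low power shows the plan to be wrong.** It does not. It limits what a retained comparison could show, and it applies equally to the baseline split suggested below.

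**Conclusion.** The point holds in limited form. Two stated analysis rules are wrong as written: a log-rank comparison with no second group or reference curve, and a median with span for categorical variables. The first leaves the choice of groups open until after the data are seen. The second needs correcting even if it is only a slip.

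The issue is minor. It concerns PFS, OS and descriptive summaries, and the clinical benefit rule (19, then 39; more than 16 successes) does not depend on either sentence. The detectable hazard ratio of about 0.41 rests on an even split, events in all 39 patients and a two-sided 5% test, none of which the article states; uneven splits or fewer events make it more extreme. The toxicity illustration rests on assumed grade distributions.

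**What to change.** Change two sentences in Statistics:

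1. Delete the log-rank comparison. Report Kaplan-Meier estimates of PFS and OS with 95% confidence intervals.
2. If a comparison is kept, restrict it to a baseline factor named before the data are examined, for example TOP1/CEN-20 ratio ≥2 versus copy-number gain only. Label it exploratory, state its low power, and do not split by response.
3. Summarise categorical variables as n (%) and continuous variables as median (range). Report toxicity as worst CTCAE grade per patient, n (%).

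The cost is a wording change, with no effect on sample size, recruitment, treatment or data collection.

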### Trial status

A total of 227 patients have been screened for *TOP1* expression and we have found 50 patients (22%) to be overexpressing *TOP1* in either primary tumor, a metastatic lesion or both*.*

To date 10 patients have been included.

Initially patients were treated with irinotecan 100 mg/m^2^ but this regimen proved too toxic as two patients withdrew due to severe diarrhoea prior to their first CT evaluation. Accordingly the protocol was amended and following the dose reduction to 75 mg/m^2^ no severe toxicities have been observed.

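### PFS and OS are assigned to an undefined evaluable population although the plan announces intention-to-treat; if evaluable requires a post-baseline CT, both are likely to be overstated

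*Protocol article*

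**What the plan says.** The Statistics section of the protocol article makes a general statement, "Intention-to-treat analysis will be performed", in the paragraph that sets out the Simon two-stage design. The next paragraph gives the survival method, "PFS and OS will be estimated using the Kaplan-Meier method and compared with a log-rank test", and closes with "PFS and OS will be assessed in the evaluable population". The word evaluable occurs nowhere else in the article and is not defined.

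Under Study objectives, CBR is primary, and "Secondary endpoints include PFS, OS and toxicity". Two of the three named secondary endpoints are therefore placed on the evaluable set.

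On assessments, the Treatment section says "CT scans are performed prior to initiation of treatment and then every 6 weeks". The Trial status section reports that "two patients withdrew due to severe diarrhoea prior to their first CT evaluation", that "To date 10 patients have been included", and that "following the dose reduction to 75 mg/m^2^ no severe toxicities have been observed". It does not say how the two withdrawals enter any analysis.

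**The concern.** The article states an analysis principle and then departs from it for PFS and OS without giving a reason. This is a stated choice of population, not a detail left for a fuller document.

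If being evaluable depends on something that happens after treatment starts, such as reaching a CT, the set is selected on early survival and tolerance. Patients who die, deteriorate or leave before week 6 would be missing from the curves. Three things follow:

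- PFS and OS would tend to look better than in the patients actually included.
- CBR would be reported on one denominator and PFS and OS on another. With a single arm, no control group shares the exclusion and offsets it.
- OS requires only vital status. Whether a patient had a scan has no bearing on whether survival can be observed.

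Kaplan-Meier estimation already accommodates incomplete follow-up through censoring, so the method gives no reason to drop these patients.

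**Working it through.** **The plan's own figures.** The article gives no number for PFS or OS. Its only design figures concern CBR: 19 + 20 = 39 patients, stop with 6 or fewer of 19, succeed with 17 or more. (The Abstract gives a total of 40; the difference does not matter here.) Reading the stated 30% as the null rate and assuming 50% as the target, which the article does not state, exact binomial calculation gives a one-sided type I error of 0.0455 and power of 0.804. A minimax search returns the same 6/19 and 16/39. None of this depends on the PFS and OS population, so the primary decision is untouched.

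**Illustration 1: excluding a share of patients with different prognosis.** Assumptions, none from the documents: exponential survival; a share *d* excluded; the excluded patients' median is *k* times the evaluable patients' median. Let *t* be the all-patient median as a multiple of the evaluable-only median. Then *t* solves

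(1 − d)·2^(−t) + d·2^(−t/k) = 0.5.

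For k = 0.5, put x = 2^(−t), giving d·x² + (1 − d)·x − 0.5 = 0:

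- d = 2/39 = 0.051: x = 0.513, t = 0.96
- d = 0.10: x = 0.525, t = 0.93
- d = 0.20: x = 0.550, t = 0.86

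The evaluable-only median is then longer by about 4%, 8% and 16% (1/t − 1, from unrounded t). Other values of *k*:

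| Excluded share | k = 0.25 | k = 0.5 | k = 1 | k = 1.5 |
|---|---|---|---|---|
| 2/39 | 0.94 | 0.96 | 1.00 | 1.02 |
| 10% | 0.87 | 0.93 | 1.00 | 1.04 |
| 20% | 0.75 | 0.86 | 1.00 | 1.08 |

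With k = 1 there is no bias; with k = 1.5 the evaluable-only figure is too low. If every excluded patient counted as a PFS event at time 0, t = 1 + log2(1 − d), which gives 0.92, 0.85 and 0.68. That is the extreme case.

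**Illustration 2: deaths before the 6-week CT.** If patients who die before time t0 are removed, the remaining curve is S(t)/S(t0), which is never below S(t). For this component the direction is fixed. Take t0 = 42 days = 1.38 months, exponential survival, and the median OS of 8.6 and 9.7 months that the Background section (irinotecan in BC) quotes from an earlier irinotecan trial:

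- Deaths before t0: 1 − 2^(−1.38/8.6) = 10.5% and 1 − 2^(−1.38/9.7) = 9.4%.
- Constant hazard means that removing them adds t0, about 1.4 months, to the median.

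The eligibility requirement of at least 3 months' life expectancy should make early deaths rarer than this, so the real shift would be smaller.

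**The case against.** The strongest reply is that evaluable is undefined. It might mean everyone who received a dose, in which case the two withdrawals stay in. Definitions of analysis sets often sit in a full protocol or SAP that is not shown, so the missing definition alone is not a fault. That stands, and it makes the point about bias conditional. It does not remove the mismatch between the two sentences, nor supply a reason to restrict OS.

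A second reply is that the intention-to-treat sentence sits with the CBR design, while PFS and OS have their own paragraph, so endpoint-specific populations may be intended. That reading is possible, but the sentence carries no such limit. Even if it was meant that way, the choice remains a poor one for OS.

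A reader might go further and infer that the two withdrawals are dropped, that both curves are biased upward, and that the effect is about 10 points: 2/10 = 20% excluded, about 8 of 39; with an assumed 50% 4-month PFS in the other 31, 15.5/39 = 39.7%. The documents do not support this:

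- The article does not say that these patients are excluded.
- Both withdrawals occurred under the initial dose. The article reports no severe toxicity since the amendment and does not say how many of the 10 received the initial dose, so 20% is not a forecast.
- The calculation counts every excluded patient as a failure. A patient censored at enrolment leaves the Kaplan-Meier estimate unchanged.
- For patients who leave because of toxicity, the sign depends on their later course, which is not reported.

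Nor does the article say that PFS or OS will be tested formally against historical figures.

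**Conclusion.** The point holds in conditional form. The intention-to-treat statement and the evaluable restriction need to be reconciled, and nothing in the article justifies the restriction for OS. If evaluable requires a post-baseline CT, overstatement of PFS and OS is likely: omitting early deaths can only raise OS, and omitting early withdrawals raises the curves if those patients do worse than the rest.

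The size cannot be derived from the documents. Excluded patients with half the median survival would put the all-patient median at about 0.86 to 0.96 times the evaluable-only median for excluded shares from 20% down to 2/39. This rests on exponential survival and on assumed shares and prognosis.

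Severity is moderate. Only secondary endpoints are affected, and the CBR decision rule stays as it is.

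**What to change.** Replace the sentence on the evaluable population with wording such as:

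> PFS and OS will be analysed in all included patients (the same intention-to-treat population as CBR), from enrolment. Patients who withdraw early stay in OS follow-up. For PFS, patients without a post-baseline CT are censored at enrolment unless they die or progress clinically; withdrawal before the first CT is counted as an event in a sensitivity analysis. An analysis in the evaluable population, with that term defined, is supportive only.

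For PFS, the main analysis then gains the early deaths and clinical progressions, while censored early leavers barely move the curve. The sensitivity analysis shows how much the result could depend on them. For OS, all included patients contribute.

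The cost is a change of wording and vital-status follow-up of early withdrawals, as far as their consent allows. With 10 patients included at the time of writing, this should still be feasible. Reported PFS and OS may be slightly less favourable. Sample size and the CBR rule do not change.
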